**Fig. 1 Fig1:**
[figure not shown]
Participant allocation to groups about here

### Variables

Table 1 shows predictors, primary and secondary outcome measures, and the assessment timepoints relating to each measure. As the table indicates, predictors are marked by a single asterisk whereas secondary outcomes are marked by a double asterisk. *Acute monitoring* (V0) refers to the time from first presentation to the emergency department to the time of consent; at which point, routinely collected data will be retrospectively retrieved from medical records. *At rehabilitation* (V1) may vary between five and 12 weeks following SCI as participants will vary with respect to the amount of time required spent in acute care prior to proceeding to rehabilitation. *Discharge* (V2) refers to a three- to four-month period following assessments completed at V1. The timepoint *in community* refers to 12-months after the date of the initial SCI.

**Table 1 Tab1:** Predictors, primary and secondary outcome measures, and assessment timepoints

Assessment time-points	Visit-type				
Study phase	Acute monitoring	At rehab		At discharge	In community
Visit number		(V0)	(V1)	(V2)	(V3)
Eligibility pre-screening (by treating Clinician)		✓			
Informed Consent			✓		
**Primary outcome**					
**Measure**	**Measurement tool**				
Cognitive functioning	NUCOG		✓	✓	✓
**Predictors* and secondary outcomes****					
**Measure**	**Measurement tool**				
Autonomic assessment*	HRV		✓	✓	✓
Current medications*	Medical records	✓	✓	✓	✓
Diagnostic evidence of TBI*	Cerebral CT/MRI scan	✓			
	GCS	✓			
	PTA	✓			
Demographics*	Medical records	✓			
Environmental factors*	Carer/family status		✓	✓	✓
	Compensation status		✓	✓	✓
Injury characteristics*	Medical records	✓			
Medical History*	Medical records	✓			
Other co-morbidities	Medical records*	✓			
	SCI SCS**		✓	✓	✓
Participation measure**	WHODAS domain				✓
Personal factors**	ADAPSS		✓	✓	✓
	Brief COPE		✓	✓	✓
	CD-RISC Short Form		✓	✓	✓
	MSES		✓	✓	✓
	WHO ASSIST		✓	✓	✓
Psychological measures**	GAD-7		✓	✓	✓
	PCL-5		✓	✓	✓
	PHQ-9		✓	✓	✓
Psychosocial measures**	Berlin Questionnaire		✓	✓	✓
	FSS		✓	✓	✓
	ISCoS pain dataset		✓	✓	✓
	PCS		✓	✓	✓
	PSQA		✓	✓	✓
	SSQ		✓	✓	✓
QoL measure**	EQ-5D-5L		✓	✓	✓
Return to work**	Questionnaire				✓
Severity of injury*	SCI: AIS and FIM	✓			
	TBI: WPTAS	✓			
Transition ED*	ED record	✓			
Vital signs*	BP, HR, RR, and Temp	✓	✓	✓	✓

*Abbreviations*: *ADAPSS* Appraisal of DisAbility Primary and Secondary Scale, *AIS* American Spinal Injury Association Impairment Scale, *BP* blood pressure, *Brief COPE* Coping Orientation to Problems Experienced, *CD-RISC* Connor-Davidson Resilience Scale, *ED* Emergency Department, *EQ-5D-5L* Euro Quality of Life 5-Dimensional 5-level, *FIM* Functional Impairment Scale, *FSS* Fatigue Severity Scale, *GAD-7* Generalized Anxiety Disorder 7-Item Scale, *GCS* Glasgow Coma Scale, *HR* heart rate, *HRV* heart rate variability, *ISCoS* International Spinal Cord Society, *MH* Mental health, *MSES* Moorong Self-efficacy Scale, *NUCOG* Neuropsychiatry Unit Cognitive Assessment Tool, *PCS* Pain Catastrophizing Scale, *PHQ-9* Patient Health Questionnaire-9, *PSQA* Pittsburgh Sleep Quality Assessment, *PTA* post-traumatic amnesia, *PCL-5* Post-traumatic Stress Disorder Checklist for the Diagnostic and Statistical Manual of Mental Disorders Firth Version, *RR* respiratory rate, *SCI* spinal cord injury, *SCI SCS* Spinal Cord Injury Secondary Condition Scale, *SSQ* Social Support Questionnaire, *TBI* traumatic brain injury, *Temp* temperature, *WHO ASSIST* World Health Organisation Alcohol Smoking and Substance Involvement Screening Test, *WHODAS* World Health Organisation Disability Assessment Scale, *WPTAS* Westmead Post Traumatic Amnesia Scale

*Predictor measure

**Outcome measure

### Measurement

#### Mode of assessment

Participants will be assessed either face-to-face or via a secure online platform called Research Electronic Data Capture (REDCap) [79]. Participants entering their responses online are given their personal REDCap link and instructions on how to complete.

#### Primary outcome measure

##### Neurocognitive testing

The Neuropsychiatry Unit Cognitive Assessment Tool (NUCOG) [80], a validated cognitive measure for SCI, will be used to screen cognitive functioning using age-adjusted normative scores provided in the administration and scoring manual to identify deviations from normal cognitive functioning. Means and SD for each of the five subscales comprising the NUCOG (attention, visuoconstructional, memory, executive, and language) permit analyses of patterns of performance across subscales. The tasks presented in each of the subscales are listed below:

Attention: Measures of orientation, forward and backward digit span, and the recitation of an overlearned sequence.

Visuoconstructional: Drawing reproduction, orobuccal and limb praxis, left-right orientation, spatially-directed attention, and calculation.

Memory: Verbal recall of words, spatial recall through the re-drawing of previously copied figures, autobiographical and other personal or historical details.

Executive function: Motor sequencing, categorical/semantic fluency, abstract thinking, and interference.

Language: Comprehension, repetition, naming, writing, reading, and word-finding.

Items requiring normal hand function (e.g., drawing reproduction) will be adapted as per previous studies where this has been shown to not alter the validity of NUCOG scores [81]. Where it is not possible to administer the NUCOG face-to-face (e.g., discharge to the community outside metropolitan areas within the state of NSW, Australia, or social distancing restrictions due to COVID-19), administration will occur via telehealth methods. Administration of the NUCOG via teleconferencing required further adjustments to the NUCOG assessment procedure to suit the telehealth environment. These procedural adjustments will be standardized, and validation will constitute part of this study.

#### Secondary measures

##### Autonomic assessment

The assessment of heart rate variability (HRV) will be incorporated into analyses of the influence of cardiovascular dysfunction on MCI. This will involve a Biosemi Active-Two System, 32 channels, at 2480 Hz sampling rate to obtain three-lead electrocardiograph recordings with Ag/AgCl electrodes positioned according to Einthoven’s triangle (beneath the right and left clavicles, and on the lower edge of left rib cage on the anterior axillary line). Additional channels will measure respiration rate (sensitive band around the chest), and skin conductance (surface electrodes on second and fourth fingers of non-dominant hand), which will be collected as indicators of sympathetic nervous system activity.

##### TBI screening

TBI will be identified at the time of presentation to the emergency department and throughout the period of medical care using the following indicators: (i) Glasgow Coma Scale scores at the time of injury and at the time of presentation to the emergency department; (ii) evidence of intracranial injuries from medical imaging; (iv) periods of post-traumatic amnesia (PTA) as assessed by the Abbreviated Westmead Post-traumatic Amnesia Scale (A-WPTAS), and/or, (v) reported periods of disorientation, confusion and/or witnessed periods of unconsciousness that is not accounted for by delirium or substance withdrawal. Additionally, participants will be interviewed at the time consent is obtained with proxy questions assessing the presence of any self-report TBI indicators that were evident at the time of injury, to corroborate diagnostic evidence available from medical records. A probabilistic approach will be used to identify the occurrence of TBI by cross-checking clinically-documented evidence of TBI against self-reported information relevant to TBI [82].

##### Self-report questionnaires

*Generalised anxiety disorder-7 (GAD-7)* [83] GAD-7 is a seven-item instrument that is used to assess the severity of generalized anxiety disorder (GAD). Items ask individuals to rate the severity of symptoms experienced over the past 2 weeks. Responses including ‘not at all,’ ‘several days,’ ‘more than half the days,’ and ‘nearly every day’ are summed to provide a total score. Total scores of 5, 10, and 15 respectively represent cut-points for mild, moderate, and severe GAD symptoms.

*Patient health questionnaire-9 (PHQ-9)* [84] PHQ-9 asks respondents to rate each of the nine Diagnostic and Statistical Manual of Mental Disorders Fourth Edition (DSM-IV) criteria for depression over a two-week timeframe. Ratings for items ranging from 0 ‘not at all’ to 3 ‘nearly every day’ are summed to determine depressive-symptom severity (0–4 no depressive symptoms; 5–9 mild depressive symptoms; 10–14 moderate depressive symptoms; 15–19 severe depressive symptoms; and 20–27 severe depressive symptoms).

*Post-traumatic stress disorder checklist for the diagnostic and statistical manual of mental disorders version V short-form (PCL-5-SF)* [85] PCL-5-SF is a 4-item abbreviation of the full 20-item PCL-5 that has been shown to reliably screen for symptoms of post-traumatic stress disorder (PTSD) [86]. Patients are asked to rate symptoms they have experienced over the past month including re-experiencing symptoms, symptoms of avoidance, negative alterations in cognition and mood, and alterations in arousal and reactivity on a 5-point Likert-type scale ranging from ‘not at all’ to ‘extremely’ often. Scores indicating a likely diagnosis of PTSD vary in accordance with the desired level of sensitivity and specificity; conservative (PCL-5 ≥ 38), liberal (PCL-5 ≥ 28), or intermediate (PCL-5 ≥ 32 or DSM-5 Criteria B-E) [85].

*Adapted version of the brief pain inventory (BPI)* [87] Three items from the Interference scale of the full Brief Pain Inventory (BPI) and one item from the severity scale of the BPI will be included to capture patients’ pain experiences. The three interference items included are those selected for inclusion in the International Spinal Cord Injury Basic Pain Data Set Version 2.0; ‘how much has your pain interfered with your: activities, mood, and night’s sleep in the last week,’ with response options ranging from 0 ‘no interference’ to 10 ‘extreme interference.’

*Social support questionnaire short form (SSQ6)* [88] SSQ-6 is a 6-item measure of social support that asks patients to indicate the number of people available to them for the provision of support, and to rate how satisfied they are with the level of support they receive. Satisfaction ratings range from ‘very dissatisfied’ to ‘very satisfied’ on a 6-point Likert-type scale.

*Pain catastrophizing scale (PCS)* [89] PCS is a self-report cognitive bias measure consisting of 13 items that screen for the presence of catastrophizing thoughts (e.g., “I can’t stop thinking about how much it hurts”) scored 0 to 4 resulting in a total possible score of 54. Scores above 30 indicate clinically significant levels of pain catastrophizing.

*Fatigue severity scale (FSS)* [90] FSS is a 9-item self-report scale that measures the severity of fatigue and its effects on activities and lifestyle. Items are scored on a 7-point scale Likert-type scale (1 = strongly disagree and 7 = strongly agree). The higher the score the more severe the fatigue.

*The Pittsburgh sleep quality index (PSQI)* [91] PSQI measures the quality and patterns of sleep in seven domains: subjective sleep quality, sleep latency, sleep duration, habitual sleep efficiency, sleep disturbances, use of sleep medication, and daytime dysfunction. Scoring of items is based on a 0 to 3 Likert scale with a score of 3 reflecting the negative extreme. Scores greater than a total of 5 indicate poor sleep.

*Spinal cord injury secondary conditions scale (SCISCS)* [92] SCISCS assesses secondary physiological conditions that are associated with SCI using a 4-point ordinal scale ranging from 0 (not experienced/insignificant problem) to 3 (significant/chronic problem). Participants are asked to rate the degree to which each of the 16 items have affected their activities and independence in the last 3 months. Examples of secondary conditions include pressure ulcers and bladder dysfunction. Total scores range from 0 to 48 with higher scores indicating greater overall problems with secondary physiological conditions.

*World Health Organisation alcohol, smoking, and substance involvement screening test (WHO ASSIST)* [93] Question 2 of the WHO ASSIST which asks about frequency of use of each of 10 substances (tobacco, alcohol, cannabis, cocaine, amphetamine-type stimulants, inhalants, sedatives, hallucinogens, opioids, and ‘other’ drugs) during the past 3 months is included as this provides critical information about the substances most relevant to current health status. Responses to this question are rated on a 5-point frequency scale ranging from ‘never’ to ‘daily or almost daily.’

*Brief coping orientation to problems experienced (brief COPE)* [94] Brief COPE is a 28-item self-report questionnaire that measures effective and ineffective ways to cope with stressful life events including reactions to serious medical diagnoses. Only questions 2, 3, 7, and 8 of the Brief COPE are included to minimise time of testing. These four questions permit calculation of scores for the ‘Active – Approach’ and ‘Avoidant – Denial’ scales.

*Moorong self-efficacy scale (MSES)* [95] MSES was developed to measure self-efficacy as it relates to the performance of functional activities of daily living in individuals with SCI. Participants rate their confidence in their ability to complete 16 tasks on a 7-point Likert-type scale with 1 = very uncertain and 7 = very certain. The higher the score, the greater perceived self-efficacy to perform functional activities.

*Connor-Davidson resilience scale (CDRS)* [96] CDRS is a 25- item self-report measure of personal resilience with higher scores reflecting greater resilience. Only questions 1 ‘able to adapt to change’ and 8 ‘tend to bounce back after illness or hardship’ are included to appraise patients’ coping over the past month or the period of acute adjustment to SCI and hospitalisation. This two-item CDRS has demonstrated internal consistency, test-retest reliability, convergent validity, and divergent validity, as well as significant correlations with the full scale [96].

Appraisals of DisAbility: Primary and Secondary Scale (ADAPSS) [97] Short-Form.

ADAPSS Short-Form is measure of SCI-specific appraisals, with a 2-factor structure of catastrophic negativity and determined resilience.

*EUROQOL version 5D-5L (EQ-5D-5L)* [98] EQ-5D-5L comprises five dimensions each describing different aspects of health: mobility, self-care, usual activities, pain/discomfort, and anxiety/depression. Each dimension has three response levels: no problems, some problems, extreme problems. Participants are asked to indicate their health status by checking the most appropriate response-level for each of the five dimensions. The digits for the five dimensions can be combined into a 5-digit number yielding a description of health.

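### The PTSD score cut-offs of 28, 32 and 38 cannot be reached on the 4-item PCL-5 described, and the EQ-5D-5L is described with three levels; the PCS maximum is also misstated

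*Protocol article*

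**What the plan says.** All three statements are in the protocol article under Secondary measures, Self-report questionnaires.

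- **PCL-5-SF.** The text names the short form and says "PCL-5-SF is a 4-item abbreviation of the full 20-item PCL-5". Patients rate symptoms "on a 5-point Likert-type scale ranging from ‘not at all’ to ‘extremely’ often"; the numeric anchors are not given. The scores offered as pointing to a likely PTSD diagnosis are "conservative (PCL-5 ≥ 38), liberal (PCL-5 ≥ 28), or intermediate (PCL-5 ≥ 32 or DSM-5 Criteria B-E", the choice depending on the sensitivity and specificity wanted. No cut-off is given for the 4-item form. Table 1 lists the PCL-5 at V1, V2 and V3 with no short-form label, and its abbreviation list expands it as "Post-traumatic Stress Disorder Checklist for the Diagnostic and Statistical Manual of Mental Disorders Firth Version".
- **EQ-5D-5L.** The description reads "Each dimension has three response levels: no problems, some problems, extreme problems". The abbreviation list under Table 1 expands the same instrument as "Euro Quality of Life 5-Dimensional 5-level".
- **PCS.** The article says "PCS is a self-report cognitive bias measure consisting of 13 items", with items "scored 0 to 4 resulting in a total possible score of 54". Totals above 30 are treated as clinically significant.

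Table 1 marks all three as secondary outcomes. Statistical methods plans repeated measures linear mixed models to compare secondary outcomes between the cognitively impaired and unimpaired groups. It also plans latent class trajectories for selected secondary measures, with anxiety, depressive mood and quality of life as examples.

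**The concern.** A cut-off is usable only if it lies within the range of the scale to which it is applied. The PTSD thresholds stand in the paragraph on the 4-item form, and no other threshold is offered. An analyst who took them as the scoring rule would classify nobody as positive on score, in either group and at any visit, whatever the symptoms. That would look like an absence of PTSD rather than a scoring fault.

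The EQ-5D point concerns data collection. Participants may answer online through REDCap (Mode of assessment). A form built to the descriptive sentence would offer three responses per dimension where the named version has five, and answers that were never offered cannot be recovered later. Quality of life is named in Secondary objectives and again in Statistical methods, so the version needs to be clear.

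The PCS maximum is a smaller matter of the same kind: the stated total does not follow from the stated items.

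**Working it through.** The check is: maximum total = number of items × top item score.

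**The plan's own figure (PCS).** Inputs: 13 items scored 0 to 4; stated maximum 54.
- 13 × 4 = 52. The stated 54 is not reproduced and is 2 points too high.
- The method is sound, because it reproduces other figures in the same section: SCISCS 16 × 3 = 48, as stated; PHQ-9 9 × 3 = 27, as stated.
- The working threshold of above 30 lies below both 52 and 54, so no classification changes.

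**PCL-5-SF.** Inputs: 4 items (full form 20) on a 5-point scale; cut-offs 28, 32 and 38. The anchors are not given, so both usual codings are taken as assumptions.

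| Coding (assumed) | 4-item range | 20-item range | 28, 32, 38 reachable on 4 items? | On 20 items? |
|---|---|---|---|---|
| 0–4 | 0 to 16 | 0 to 80 | none | all |
| 1–5 | 4 to 20 | 20 to 100 | none | all |

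- Mean item score needed on four items: 28/4 = 7, 32/4 = 8, 38/4 = 9.5. No 5-point item under either coding exceeds 5.
- Items at top score needed to reach the lowest cut-off: 28/4 = 7 under 0–4 coding; 28/5 = 5.6, so 6, under 1–5 coding. The form has 4.

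The conclusion is the same under either coding. The cut-offs fit the range of the 20-item form.

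**EQ-5D-5L.** The name and the abbreviation list say five levels; the description says three. Over five dimensions, three levels give 3^5 = 243 profiles and five give 5^5 = 3125. These counts show that the two are different instruments; they do not measure an effect on any planned result.

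**The case against.** **The cut-offs may be background only.** They are labelled PCL-5, not PCL-5-SF. The sentence lists three alternatives, adopts none, and does not say that participants will be classified. Nothing in Statistical methods plans a PTSD caseness analysis. Linear mixed models would ordinarily take the total score, and PTSD is not among the named examples for trajectories. This stands. A reader might infer that the plan makes PTSD caseness 0% in both groups at every visit, and the document does not support that: it shows only what would follow if someone applied these cut-offs to the 4-item total.

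**The intermediate rule has a route that needs no score.** It allows DSM-5 Criteria B–E as an alternative. A reader might infer that nobody could screen positive by any route, or that four items cannot address those criteria. Neither is shown. The article names four symptom groups for the four items and does not say what each criterion requires, so arithmetic does not close this route.

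**Table 1 could mean the full form.** The cut-offs would then be reachable, but Table 1 and Self-report questionnaires would disagree on which instrument is given. The reply moves the defect without removing it.

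**The EQ-5D error may be one faulty sentence.** The name, Table 1 and the abbreviation list all say 5L. The REDCap form is not shown, and the article mentions only a five-digit health description, with no value set. A reader might infer that data have been or will be collected on the wrong version; that cannot be concluded. The contradiction in the text remains.

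**The PCS slip changes nothing in use.** Agreed.

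**Conclusion.** The point holds as a set of scoring errors in the text for secondary outcomes, of minor to moderate severity.

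- The three PTSD score cut-offs exceed the 4-item maximum of 16 or 20 by at least 28 − 20 = 8 points. Classification on score by any of them would find no positives on that form. This assumes coding of 0–4 or 1–5 and that the short form is the one given, as Self-report questionnaires says. A continuous analysis of the total would be unaffected.
- The EQ-5D-5L description contradicts the instrument's name. Whether it matters for the data depends on the form in use, which the article does not show.
- The PCS maximum is overstated by 2 points, with no effect on scoring or classification.

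The NUCOG primary outcome, the allocation to groups and the sample size are untouched.

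**What to change.** 1. Reconcile Table 1 and Self-report questionnaires on which PCL-5 form is given, and use the same label in both.
2. State that the PCL-5 total on that form is analysed as a continuous score under the planned mixed model. Remove the 28/32/38 cut-offs, or replace them with a cut-off validated for the form used. Whether one exists for the 4-item form cannot be checked from the article.
3. Correct the EQ-5D description to the version used, and check that the REDCap form offers the matching number of levels.
4. Change the PCS maximum from 54 to 52.

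The cost is a few edits to the scoring text and one check of the REDCap form. No new data are needed for the text corrections.

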### Bias

Several processes will help to reduce bias in the analyses. First, only adults with a new SCI will be recruited into the study. Second, inclusion and exclusion criteria will be strictly adhered to reduce unwanted confounding of data. Third, medical information such as PTA testing undertaken in the first 24 to 48 h after the SCI that informs the presence of mild TBI, as well as other relevant measures and TBI proxies, will be harvested from medical records to confirm the presence of a mild TBI, permitting the differentiation of TBI from other predictors of MCI. Fourth, to minimize loss to follow-up, multiple options for assessment will be provided, including online assessment, face-to face paper assessment, teleconference, and telephone assessment. Follow-up reminders by email or telephone texts will be incorporated to enhance adherence to study participation. Fifth, the use of linear mixed model repeated measures will reduce the impact of loss of missing data.

### Study size

Our preliminary study of 150 adults with SCI [14] found a 10-point difference in the NUCOzG total mean scores (with a SD of 6.3) between the participants with MCI (*n* = 60) versus those without (*n* = 90). Therefore, the resultant effect size was large being > 1.5. For this prospective study, to test the primary outcome of interest, we are conservatively assuming a between-groups moderate Cohen’s d effect size of 0.7, a group allocation of 0.6:1 MCI: non-MCI, an alpha of 0.05, 80% statistical power, three assessment points, a compound symmetry correlation matrix (rho = 0.5), and attrition rates of 20 and 30% between assessment points. The estimated required overall sample size is at least 90 participants. This calculation was based on linear mixed model of repeated measures with a general correlation structure and the estimated sample size includes limited interaction effects [99].

